### Secondary outcome

#### Clinical outcome

Time to clinical improvement (TTCI) [time frame: up to 28 days]
A.Time to clinical improvement (TTCI) was defined as time from randomization to a decline of 2 categories on the seven-category ordinal scale of clinical status or live discharge from the hospital, whichever came firstClinical status assessed by 7-category ordinal scale on days 7, 14, and 28Change in National Early Warning Score (NEWS) from baseline to day 28 [time frame: day 1 through day 28]*The NEW score has demonstrated an ability to discriminate patients at risk of poor outcomes. This score is based on 7 clinical parameters (respiration rate, oxygen saturation, any supplemental oxygen, temperature, systolic blood pressure, heart rate, level of consciousness). The NEW Score is being used as an efficacy measureTime to National Early Warning Score (NEWS) of ≤ 2 and maintained for 24h 28 [time frame: day 1 through day 28]Duration of hospitalization [time frame: day 1 through day 28] measured in daysDuration of new non-invasive ventilation or high flow oxygen use [time frame: day 1 through day 28]Incidence of new non-invasive ventilation or high flow oxygen use [time frame: day 1 through day 28]Duration of new supplement oxygen use [time frame: day 1 through day 28]Incidence of new supplement oxygen use [time frame: day 1 through day 28]Duration of new ventilator or extracorporeal membrane oxygenation (ECMO) use [time frame: day 1 through day 28]Incidence of new ventilator or extracorporeal membrane oxygenation (ECMO) use [time frame: day 1 through day 28]Mortality at day 28 [time frame: day 1 through day 28]. Date and cause of death (if applicable)Time (days) from treatment initiation to death

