#### Virological endpoints

1. Proportions of patients with a negative nasopharyngeal swab and sputum sample for SARS-CoV-2 quantitative RT-PCR on days 3, 7, 10, 14, and 21 after starting treatment

2. Viral load change (log10 viral load) of nasopharyngeal swab and sputum sample for SARS-CoV-2 quantitative RT-PCR on days 3, 7, 10, 14, and 21 after starting treatment

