## Statistical methods

### Statistical methods for primary and secondary outcomes {20a}

Intention-to-treat analysis and per protocol analysis will be conducted respectively, and intention-to-treat analysis will be performed as the main analysis.The categorical variable of the evaluation index will be analyzed using Pearson’s chi-square test, and the continuous variable will be analyzed using ANOVA or Kruskal–Wallis test.The virus removal rate on day 14, one of the secondary outcomes, will be analyzed using Pearson’s chi-square test.Time to clinical improvement will be assessed on all subjects by day 28. If there is no clinical improvement or a case of death by day 28, it will be recorded as day 28, and analyzed by Kaplan–Meier plot and log-rank test.

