## Methods in analysis to handle protocol non-adherence and any statistical methods to handle missing data {20c}

Outcome data obtained from all randomized participants will be included in the main analyses to prevent attrition bias. To prevent missing data, the researcher, trained research nurse, and research assist will double check the data as well as the recording of reasons for missing data. By replacing missing data with the mean or median value, we plan to analyze with minimal data loss.

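### The mean/median replacement rule makes no exception for death, so day-28 NEWS change, and possibly day-14 virus removal, is biased toward the arm with more deaths

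*Protocol article*

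**What the plan says.** All references are to the protocol article.

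- **Tests.** Section {20a} makes intention-to-treat the main analysis. For continuous outcomes, "the continuous variable will be analyzed using ANOVA or Kruskal–Wallis test". For virology, "The virus removal rate on day 14, one of the secondary outcomes, will be analyzed using" Pearson's chi-square test.
- **Death rule.** The same section has one, for time to clinical improvement: "If there is no clinical improvement or a case of death by day 28, it will be recorded as day 28". It gives none for NEWS or virus removal.
- **Endpoints.** The clinical outcome list defines NEWS change from baseline to day 28 and says of NEWS: "This score is based on 7 clinical parameters". The virological endpoint is "Proportions of patients with a negative nasopharyngeal swab and sputum sample for SARS-CoV-2 quantitative RT-PCR" on a list of days that includes day 14.
- **Missing data.** Section {20c} says "Outcome data obtained from all randomized participants will be included in the main analyses", and then: "By replacing missing data with the mean or median value, we plan to analyze with minimal data loss". No exception is made for death.
- **Where death is already handled.** On the seven-category scale, death is the last category. The primary outcome requires live discharge or a decline of 2 categories. Day-28 mortality and time to death are separate secondary outcomes.

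**The concern.** NEWS is built from bedside measurements, so it does not exist for a patient who has died. A patient who died before day 14 has no day-14 sample. A mean or median taken from observed patients gives such a patient a survivor's value, and leaving the patient out gives a comparison of survivors. In both cases the worst possible result is treated as neutral or good.

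Deaths are foreseeable. Inclusion starts at category 3 with no upper limit short of death, only patients judged at high risk of death within 3 days are excluded, and mortality is itself an outcome.

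The article describes NEWS as an efficacy measure and puts viral suppression in its main hypothesis. If the drug raised mortality, its arm could look better on both endpoints. If it lowered mortality, the sicker survivors it kept alive would count against it.

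**Working it through.** **No plan figure to reproduce.** The article gives no expected NEWS change, clearance rate or death rate. Only the 42 patients per arm come from it. Every other input below is an assumption chosen to show direction and range.

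**Step 1: what each rule does to a death.**

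| Endpoint | Death rule stated | Value under {20c} replacement | Value if only obtained data are used |
|---|---|---|---|
| Primary outcome, ordinal status | By definition (category 7, live discharge) | Not needed | Not needed |
| Time to clinical improvement | Recorded as day 28 | Not needed | Not needed |
| NEWS change to day 28 | None | Mean or median of observed patients | Left out |
| Virus removal, day 14 | None | Majority observed result | Left out |

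**Step 2: day-14 virus removal, worked counts.** Assume 25 of 42 patients removed in each arm, 2 control and 5 nafamostat deaths before day 14, and no one who died among the 25.

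- Survivors only: control 25/(42 − 2) = 25/40 = 62.5%; nafamostat 25/(42 − 5) = 25/37 = 67.6%; difference +5.1 points.
- Median fill-in (the observed majority is negative): control (25 + 2)/42 = 27/42 = 64.3%; nafamostat (25 + 5)/42 = 30/42 = 71.4%; difference +7.1 points.
- All randomized, dead counted as not removed: 25/42 = 59.5% in both arms; difference 0.

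The first two differences are far from significance (p = 0.64 and p = 0.48). If most observed patients were positive, the median would be positive, the dead would count as not removed, and fill-in would cause no such inflation.

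**Step 3: NEWS change, simulation.** Inputs: 42 per arm; latent change with mean −3 and SD 2.5 in both arms, so no drug effect on NEWS; death correlated with a poor change; t-test (two-group ANOVA) at one-sided 0.05. Several thousand runs per scenario.

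| Mortality, control v nafamostat | Correlation | Spurious advantage to nafamostat, survivors only | One-sided false-positive rate |
|---|---|---|---|
| Equal | 0.7 | 0 | about 5% |
| 2% v 5% | 0.7 | 0.10 points | about 7% |
| 5% v 12% | 0.3 | 0.09 points | about 7% |
| 5% v 12% | 0.7 | about 0.2 points | 10–11% |
| 5% v 20% | 0.7 | about 0.4 points | about 19% |
| 12% v 5% | 0.7 | about −0.2 points (a penalty) | – |

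Mean fill-in gives nearly the same as leaving the dead out: 0.21 against 0.23 points in one run of the 5% v 12% case at correlation 0.7. With a two-sided test, that case gives a significant result in the wrong direction 5.8% of the time, against a nominal 2.5%.

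The equal-mortality row shows that the excess comes from unequal deaths, not from the test itself.

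**Step 4: the repair.** With deaths ranked below every survivor and a one-sided rank test, the rate of false claims of benefit at correlation 0.7 is about 3% for 5% v 12% mortality and about 1% for 5% v 20%.

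**The case against.** The strongest reply is that this is a condensed article. Death handling for two secondary endpoints is usually left to the full protocol or SAP, and section {20c} does not mention death. That would settle the matter if the article were silent. It is not: it fixes a replacement rule with no exception, beside a death rule confined to one endpoint.

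Several other points stand and limit the concern.

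- **Virus removal.** A reader might infer that the plan necessarily drops or fills in the dead here. The article does not support that. Under intention-to-treat, a proportion of patients with a negative sample can be read as having all randomized patients in the denominator, and a dead patient then already counts as not removed. The concern is that {20c} allows another result.
- **Primary outcome.** A reader might infer that the main conclusion is biased. It is not, because death can never count as improvement.
- **Superiority margin.** A reader might set the +5.1 points in Step 2 against the 5% margin. That margin belongs to the primary outcome.
- **Inputs.** The article plans for 90% improvement on nafamostat, which leaves 10% unimproved for any reason. Mortality of 12% or 20% in that arm is above this. One-sided 0.05 is stated only for the sample size.
- **Separate reporting.** Mortality is an outcome of its own, so a large excess of deaths would be visible beside these results.
- **Choice of repair.** Counting a death as not removed mixes mortality into a virological measure. It is one defensible choice among several.

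**Conclusion.** The concern holds for NEWS change under either way of applying {20c}: replacement and omission both favour the arm with more deaths, provided those who die would have had poorer values. For day-14 virus removal it is a possibility the wording leaves open. Fill-in inflates removal only if most observed patients are negative, and an intention-to-treat denominator would avoid the problem.

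The size cannot be stated from the article. On the assumed inputs it runs from about 0.1 NEWS points and a 7% one-sided false-positive rate to about 0.2 points and 10%, and to 0.4 points and 19% under a mortality gap larger than the plan's own assumptions suggest. With equal mortality there is no inflation.

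The affected endpoints are secondary. The point should be corrected before analysis, but it does not threaten the primary comparison.

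**What to change.** 1. In {20c}, state that death is not missing data and is never replaced by a mean or median.
2. In {20a}, state that for NEWS change, patients who die before day 28 are ranked below all survivors, and the arms are compared with the Kruskal–Wallis test the section already allows.
3. In {20a}, state that day-14 virus removal uses all randomized patients as the denominator, with those who died before the sample counted as not removed.
4. Show survivors-only values for both endpoints as description.

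This takes a few sentences and no new data. The cost is in interpretation: the NEWS result becomes a rank comparison that includes death, so a mean difference can be given only descriptively for survivors, and the virology rate partly reflects mortality. Both should be read beside the separately reported mortality.

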### Interim analyses {21b}

There is no interim analysis planned yet.

## Methods for additional analyses (e.g., subgroup analyses) {20b}

There is no interim analysis planned yet.

## Methods in analysis to handle protocol non-adherence and any statistical methods to handle missing data {20c}

Outcome data obtained from all randomized participants will be included in the main analyses to prevent attrition bias. To prevent missing data, the researcher, trained research nurse, and research assist will double check the data as well as the recording of reasons for missing data. By replacing missing data with the mean or median value, we plan to analyze with minimal data loss.

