## Outcomes {12}

### Primary outcome

The primary outcome is as follows: proportion of patients with clinical improvement as defined by live discharge from hospital or a decline of 2 categories on the seven-category ordinal scale of clinical status [time frame: day 14 and day 28]

*Seven-category ordinal scale of clinical status
Not hospitalized with resumption of normal activities;Not hospitalized, but unable to resume normal activities;Hospitalization, not requiring supplemental oxygen;Hospitalization, requiring supplemental oxygen;Hospitalization, requiring nasal high-flow oxygen therapy and/or noninvasive mechanical ventilation;Hospitalization, requiring extracorporeal membrane oxygenation and/or invasive mechanical ventilation;Death.

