#### Participants withdrawal

The patient has the right to voluntarily discontinue participation in the trial for any reason at any time, and the investigator also has the right to discontinue the patient’s participation in the trial at any time.

Reasons for discontinuing participation in a clinical trial may include, but are not limited to:
Withdrawal of consent from patientsTermination of testing or closing of testing institutionsNon-compliance of patients defined as non-compliance with the clinical trial plan requirements according to the decisions of the tester or clientOccurrence of serious adverse events

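### The mean-or-median rule for missing data does not suit the binary primary outcome and, if applied within arm, understates standard errors for continuous outcomes

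*Protocol article*

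**What the plan says.** The rule is in the Protocol article, item {20c}: "By replacing missing data with the mean or median value, we plan to analyze with minimal data loss". It comes shortly after the statement that "Outcome data obtained from all randomized participants will be included in the main analyses to prevent attrition bias". It does not choose between mean and median, does not say whether the value is taken within arm or over both arms, and limits itself to no type of variable.

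The surrounding plan is as follows.

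- **Primary outcome:** "proportion of patients with clinical improvement as defined by live discharge from hospital or a decline of 2 categories" on the seven-category scale, at day 14 and day 28.
- **Tests (item {20a}):** "The categorical variable of the evaluation index will be analyzed using Pearson’s chi-square test", and "the continuous variable will be analyzed using ANOVA or Kruskal–Wallis test".
- **Analysis set (item {20a}):** "intention-to-treat analysis will be performed as the main analysis".
- **Time to clinical improvement (item {20a}):** this outcome alone has its own rule: "If there is no clinical improvement or a case of death by day 28, it will be recorded as day 28".
- **Sample size {14}:** 42 per arm, rates of 80% and 90%, a 5-point margin, one-sided alpha of 0.05, and 5% dropout in each arm.
- **Participants withdrawal:** the list introduced by "Reasons for discontinuing participation in a clinical trial may include" includes non-compliance and serious adverse events. The investigator may also end a patient's participation at any time. The trial is open label.

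**The concern.** This is a stated rule, so it is not a detail left to an analysis plan; an analysis plan would have to contradict it. It raises three problems.

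1. On a yes/no outcome with a success rate well above one half, a median fill is the same as declaring the missing patients successes. A mean fill gives a value that is neither yes nor no.
2. On a continuous outcome, inserted constants are counted as real observations. If they are taken within arm, the sample looks larger and less variable than it is.
3. Participation can end for reasons related to how the patient is doing, and the allocation is known. The filled values may therefore be wrong in a systematic way, and more often in one arm.

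At stake is whether the main intention-to-treat comparison can be trusted if follow-up is incomplete and uneven.

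**Working it through.** **Inputs.** From Sample size {14}: n = 42 per arm, rates 0.80 and 0.90, dropout 5% in each arm. The figure of 42 is taken as given; whether it follows from its own inputs is a separate matter. Unequal splits and 10% missing are assumptions, since the document gives neither.

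**Planned number missing.** 0.05 × 42 = 2.1, so about 2 per arm and 40 observed.

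**What the rule does to the primary outcome.** Code improved as 1. With 40 observed, the probability that the sample median is 1 exceeds 0.9999 at either rate. Every missing patient becomes improved, whether the median is taken within arm or overall. The mean is 0.8 or 0.9; rounded, it also becomes 1.

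**Equal missingness, 2 per arm, 32/40 v 36/40 observed.**

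| Handling of the missing | Control | Nafamostat | Difference | Two-sided p |
|---|---|---|---|---|
| Observed cases | 32/40 | 36/40 | 10.0 points | 0.210 |
| Median fill (all improved) | 34/42 | 38/42 | 9.5 points | 0.212 |
| All not improved | 32/42 | 36/42 | 9.5 points | 0.266 |
| Control improved, nafamostat not | 34/42 | 36/42 | 4.8 points | 0.558 |
| Control not, nafamostat improved | 32/42 | 38/42 | 14.3 points | 0.079 |

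In expectation the filled rates are 0.95 × 0.80 + 0.05 = 0.81 and 0.95 × 0.90 + 0.05 = 0.905, again 9.5 points apart. With no true effect and 2 missing at random per arm, simulated one-sided type I error stays at about 0.05.

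**Unequal missingness, no true effect (80% in both arms), control v nafamostat (assumed splits).**

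- Missing at random, 2 v 4: expected difference = (38 × 0.8 + 4)/42 − (40 × 0.8 + 2)/42 = 0.4/42, about 1.0 point. Simulated one-sided type I error is 0.063, rising to 0.078 at 2 v 6.
- Missing patients all truly not improved, 2 v 4: expected difference = 4/42 − 2/42, about 4.8 points. Simulated one-sided type I error is about 0.16. At 2 v 6 it is about 0.43.

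The effect is symmetrical: with the splits reversed, the bias favours control.

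**Continuous outcomes (NEWS change, log10 viral load).** Suppose k of n values per arm are filled with that arm's mean, leaving r = n − k observed. The ratio of nominal to correct standard error is √[(r − 1)/(n − 1)] × √(r/n), close to 1 − k/n.

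- k = 2 (5%): √(39/41) × √(40/42) = 0.952; two-sided type I error about 0.063.
- k = 4 (10%): √(37/41) × √(38/42) = 0.904; two-sided type I error about 0.076.

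This needs a within-arm fill. If the overall mean is used with a missing share m in both arms, the difference is multiplied by (1 − m). Its variance is then (1 − m)² × 2σ²/[n(1 − m)] = (1 − m) × 2σ²/n, which matches the nominal variance. The test keeps its level, but the effect is diluted by m.

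**The case against.** The strongest reply is that a mean or median fill is naturally a rule for numeric variables, that primary status will seldom be unknown, and that the planned loss is small and equal. Much of this stands. Live discharge counts as success, death is category 7, and other patients are in hospital. The article also promises reasonable efforts to follow everyone for the whole study. At 2 missing per arm, the criticised rule and a not-improved rule give the same 9.5-point difference. What does not stand is the limit to numeric variables: item {20c} does not state one, and it is placed beside a sentence about outcome data in the main analyses.

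Four stronger readings are tempting but not supported.

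- **That the fill shifts the result by the whole superiority margin.** Scoring 2 of 42 one way or the other moves one arm's rate by about 5 points. The margin and the assumed effect are differences between arms, and an equal shift cancels.
- **That removals for serious adverse events fall only in the nafamostat arm.** This joins the drug-related definition in Adverse event reporting and harms {22} to a permissive list covering all participants. The data collection section (item {18a}) gathers reactions in both groups. A heavier loss in one arm is possible, not established.
- **That patients removed for toxicity will be counted as recovered.** The withdrawal section does not say that outcome collection ends, and item {11b} treats stopping the drug separately.
- **That the time-to-improvement rule already settles unknown status unfavourably.** It covers absence of improvement and death, not unknown status.

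**Conclusion.** The concern holds in a limited form. The stated rule is unsuitable for the binary primary outcome: a median or rounded-mean fill makes every missing patient a success, and an unrounded mean cannot be tabulated. For continuous outcomes it understates the standard error by about 5% at 5% missing and 10% at 10% missing, if applied within arm; applied overall, it dilutes the effect instead.

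At the planned equal 5% dropout the consequence for the primary comparison is a slight dilution, 10 to 9.5 points, with type I error near nominal. Bias in favour of one arm requires missingness that is unequal or, together with that, related to poor outcome. The withdrawal section and the open-label design allow this but do not show that it will happen. The type I error of about 0.16 rests on assumed inputs: 2 v 4 missing, all truly not improved, and 80% in both arms.

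The rule should still be replaced, because it protects least where protection is needed and the change is cheap.

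**What to change.** 1. **Item {20c}:** delete the mean-or-median sentence.
2. **Primary outcome:** count unknown status at the time point as not improved. This is itself a constant imputation and works against the arm with more missing data: at 80% in both arms and 2 v 4 missing at random, (38 × 0.8 − 40 × 0.8)/42 = −3.8 points. Add multiple imputation or a tipping-point analysis as sensitivity.
3. **Continuous outcomes:** use a mixed model or multiple imputation. Add a separate rank-based analysis that places deaths worst, as sensitivity and not combined with the model.
4. **Participants withdrawal:** state that participants discontinued for any reason other than withdrawal of consent still have vital status and ordinal category recorded to day 28.

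The cost is a few sentences, a little more analysis, and a status check for a handful of patients. Estimated response rates will be slightly lower.

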## Plans to give access to the full protocol, participant-level data, and statistical code {31c}

No later than 3 years after the collection of the 1-year post-randomization interviews, we will deliver a completely deidentified dataset to trial registries for sharing purposes.

## Oversight and monitoring

### Composition of the coordinating center and trial steering committee {5d}

Not applicable

### Composition of the data monitoring committee, its role and reporting structure {21a}

The Data Monitoring Committee (DMC) has not been established. Although DMC is strongly recommended in other clinical studies with significant safety concerns in which double-blind treatment is assigned, this trial is a phase 2 clinical study with confirmed drug safety and is an open label trial, not a double-blinded study. In the pandemic caused by SARS-COV-2, an effective treatment was not established, and the study was conducted in consideration of the exceptional situation in which a therapeutic agent is urgently needed.

